**Methods/design:**

This prospective, cluster-randomised, single-blind, parallel-group, multicentre trial evaluates the morbidity and consequent socio-economic costs of the management of patients experiencing an HAE attack by a dedicated call centre as compared to usual practice. The trial aims to recruit 200 patients. Patients in the intervention arm are provided with an SOS-HAE card with the call centre’s freephone number that they can access in the case of an attack. The centre’s mission is to provide recommended expert advice on early home treatment. The centre can route the call to a local emergency medical service with competency in HAE management or even arrange for the drugs needed for the specific treatment of an HAE attack to be sent to the emergency department of the local hospital. The primary outcome measure is the number of hospital admissions for an HAE attack. Each patient will be followed up every 2 months for 2 years. The study has been approved by the ethics committee (*Comité de Protection des Personnes d’Ile de France 10*; registration number: 2012-A00044-39; date of approval: 19 January 2012).

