### Outcome measures

#### Primary outcome

The primary outcome is the number of admissions for angioedema attacks per patient per year over a 2-year period. The number of admissions for angioedema attacks is measured from the randomisation date until the end of follow-up or death. For patients discharged alive, information on the primary outcome will be collected by phoning the patients. All admission observation charts are collected and collated.

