### Sample size calculation

The aim of this study is to demonstrate a difference in outcome between a methodical management strategy and usual practice. Our primary hypothesis is that an SOS-HAE call centre might benefit patients suffering from an angioedema attack. The sample size calculation is based on the primary outcome, i.e. on the number of admissions for angioedema attacks.

A recent study involving 193 patients with HAE in France reported a rate of approximately 8 attacks/year/patient with approximately 11 % of patients coming to the ED or being admitted to hospital (i.e. an estimated 88 % per year). We hypothesise that implementation of the SOS-HAE call centre management strategy should reduce this rate by 20 %, resulting in a rate of 68 % of ED visits or admissions per year over a 2-year period. If we consider the design effect due to cluster randomisation as relatively low (1.4), the estimated required sample size is 100 patients/arm for 85 % power and a 5 % alpha risk (two-sided comparison).

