#### Analysis of primary outcome

The number of admissions for angioedema attacks will be analysed in the intent-to-treat population.

Because some patients may be blood relatives and because data from within the same family are not independent, the analysis will use generalised mixed models with the family included in the model as a random effect, the strategy as a fixed effect and with a binomial distribution of the variable of interest.

All tests will be two-sided.

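### The primary outcome is an admission count per patient-year, but the stated binomial model has no binary endpoint, number of trials or exposure term and so does not estimate that rate

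*Protocol article*

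**What the plan says.** All places are in the protocol article.

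- **Primary outcome:** "The primary outcome is the number of admissions for angioedema attacks per patient per year over a 2-year period". The count "is measured from the randomisation date until the end of follow-up or death".
- **Abstract, Methods/design:** "Each patient will be followed up every 2 months for 2 years", so the planned window is the same for everyone.
- **Analysis of primary outcome:** "The number of admissions for angioedema attacks will be analysed in the intent-to-treat population". The model is a generalised mixed model with strategy as fixed effect and family as random effect, "with a binomial distribution of the variable of interest".
- **Sample size calculation:** said to rest on the number of admissions. A previous French study "reported a rate of approximately 8 attacks/year/patient". Combined with 11% this becomes "i.e. an estimated 88 % per year" for usual practice, with the intervention "resulting in a rate of 68 % of ED visits or admissions per year over a 2-year period". The result is 100 patients per arm for 85% power, two-sided 5% alpha and a design effect of 1.4.

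**The concern.** The outcome section describes a recurrent-event count with a time denominator. The analysis section gives that same count a distribution meant for a number of successes in a known number of trials. The two fit together only if the outcome is changed, and the article does not say how. Two changes are possible:

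- **Any admission, yes or no.** A patient admitted five times counts the same as one admitted once. A patient who dies or withdraws early counts the same as one observed for 2 years.
- **Admissions out of attacks.** Repeat admissions are kept, but the result is a probability per attack. The number of attacks arises after randomisation, and this is not the per-patient-year rate in the outcome section.

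At stake is what the confirmatory analysis of the only primary outcome estimates. As the text stands, that could be settled after the data are seen.

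**Working it through.** **1. Where 100 per arm comes from.** Inputs from Sample size calculation: 0.88 and 0.68, two-sided 5%, 85% power, design effect 1.4. Treat them as two proportions with unpooled variance:

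n = (1.960 + 1.036)² × [0.88×0.12 + 0.68×0.32] / 0.20² = 8.978 × 0.3232 / 0.04 = 72.5; × 1.4 = 101.6, i.e. 102 per arm.

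The arcsine formula gives 73.3 × 1.4 = 102.6, i.e. 103. Both are within 3% of 100. The pooled formula gives 107 and the continuity-corrected one 121. So the sample size was reached, approximately, by comparing proportions.

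**2. What 0.88 is.** It is 8 attacks per patient-year × 0.11 = 0.88 events per patient-year, which is a rate. It covers emergency department visits or admissions, not admissions alone.

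**3. What any/none does to such a rate.** Assume Poisson counts and 2 full years. The control mean is 2 × 0.88 = 1.76.
- P(at least one) = 1 − exp(−1.76) = 82.8%
- P(two or more) = 1 − exp(−1.76) × (1 + 1.76) = 52.5%
- Share of control events that any/none registers = 0.828 / 1.76 = 47%

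In the intervention arm the mean is 1.36 and P(at least one) = 1 − exp(−1.36) = 74.3%.

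**4. Power of the two analyses at those rates.** Effective n per arm = 100 / 1.4 = 71.4.
- Any/none, 82.8% vs 74.3%, two-proportion test: power 23%.
- Rate comparison: ln(0.88/0.68) = 0.258; variance term 1/1.76 + 1/1.36 = 1.303; standard error √(1.303/71.4) = 0.135; power = Φ(0.258/0.135 − 1.960) = Φ(−0.051) = 48%.

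**5. How far this depends on the admission rate.** The article gives no admission rate. Keep the rate ratio at 0.68/0.88 = 0.773 and the other assumptions, and vary the control rate:

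| Control rate per year | Basis | Any/none power | Rate power |
|---|---|---|---|
| 0.88 | sample size section, visits or admissions | 23% | 48% |
| 0.52 | 0.88 × 0.59, using the share admitted in one retrospective study cited in the Discussion; illustrative | 21% | 31% |
| 0.30 | illustrative | 16% | 20% |
| 0.12 | close to 11% of patients per year, −ln(1 − 0.11) = 0.117 | 10% | 10.5% |

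**6. Sample size on the count scale.** n = 8.978 × [1/1.76 + 1/1.36 + 2k] / 0.258² × 1.4, where k is the negative binomial dispersion (not in the article, assumed):

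| k | n per arm | Rate power at 100 per arm | Any/none power |
|---|---|---|---|
| 0 (Poisson) | 247 | 48% | 23% |
| 0.5 | 436 | 30% | 15% |
| 1 | 625 | 22% | 11% |
| 2 | 1003 | 16% | 8% |

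**The case against.** **The word may be a slip for negative binomial.** That is possible, but nothing in the article shows it, and a sample size built on proportions points the other way. If it is a slip, the sentence still needs correcting.

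**A binomial model can hold repeat admissions and exposure.** This stands. With attacks as trials, repeat admissions are kept, and the data collection section records attacks and their treatment. A complementary log-log link with a log-time offset would handle follow-up time for a yes/no endpoint. A reader might infer that no binomial model could cope; the article supports only that the model as stated does not. Neither variant is specified, and neither yields the rate in the outcome section.

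**Attack recording may differ by arm.** A reader might infer that an attacks denominator is biased because intervention patients are told to call at onset. That is a risk, not something the article states: the collection schedule is the same for both arms, and an instruction to call does not show that patients do. The post-randomisation denominator is a difficulty without it.

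**Unequal follow-up may be small.** Two years are planned for all, so exposure differs only through death or withdrawal, whose frequency is not given. The problem affects the any/none reading, and its size is unknown.

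**Dichotomising halves the power.** A reader might take this from the 0.88 line. It holds there, but that rate includes emergency department visits; at 0.12 per year the loss is almost nil.

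**An article condenses the full protocol.** True, but the point rests on two statements that the article makes and that do not fit each other, not on an omitted detail.

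**Conclusion.** The point holds as a mismatch between the stated outcome and the stated model. The outcome is a rate of repeated events, and the binomial model as written does not estimate it. The sample size section shares the binary reading, since 100 per arm is recovered only by treating 0.88 and 0.68 events per year as proportions.

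The cost in power of an any/none analysis runs from about half to almost nothing over control rates from 0.88 to 0.12 per year. That range assumes Poisson counts, a rate ratio of 0.773, full 2-year follow-up and a design effect of 1.4. Whichever end applies, the stated 85% does not carry over to a count analysis: at the protocol's own rates it is about 48% under Poisson and lower with overdispersion. Admissions alone can be no more frequent than visits and admissions together, so at the same rate ratio 48% is on the favourable side.

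**What to change.** 1. **Analysis of primary outcome:** replace the binomial distribution with a negative binomial (or overdispersed Poisson) mixed model, log link, log of each patient's follow-up time as offset. Keep strategy as fixed effect and family as random effect. Report the admission rate ratio with its 95% confidence interval.
2. **Sample size calculation:** restate the power for 100 per arm on the count scale, for admissions alone, with the assumed admission rate and dispersion given as a range.

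If the sponsor really intends a yes/no endpoint, the coherent alternative is to redefine the primary outcome explicitly and align all three sections to it. That gives up the rate as the primary quantity.

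The change is to text in two sections and needs no new data, since admissions and follow-up are already collected. The Trial status section says recruitment is complete, so the restated power describes the trial and does not resize it. The price is a less favourable power statement. Whether the model also needs a random effect for centre is a separate question.

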#### Analysis of secondary outcomes

Secondary outcomes will be analysed using a mixed model ANOVA. The family will be introduced into the model as a random effect. All tests will be two-sided.

Number of admissions for a cause other than an angioedema attack per year for 2-year-period, mortality from an angioedema attack, mortality from another cause, number of ICU admissions per year, number of ED admissions per year, number of hospital stays, number of intubations per year, number of interventions by EMS, number of working days lost (and duration), costs (hospital and ambulatory costs) of patient care and SF-36 will all be estimated in each arm for 2 years.

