#### Health economics data

Call centre costs include freephone, training of EMS personnel and answering of calls (time spent and number of calls).

Patient care costs include consumption of hospital resources (admissions) and out-of-hospital resources (ED visits or emergency ambulance, drugs to treat attacks and their administration by physicians or nurses), working days lost and any remaining costs supported by patients.

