#### Secondary outcomes

Secondary outcomes are the number of admissions for a cause other than an angioedema attack per year over a 2-year period, mortality from an angioedema attack, mortality from another cause, number of ICU admissions per year, number of ED admissions per year, number of hospital stays, number of intubations per year, number of interventions by EMS, number of working days lost and their duration, costs of patient care and SF-36 score.

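### One Gaussian mixed model ANOVA is fixed for all secondary outcomes, including deaths and rare counts, and the only cost outcome leaves the call centre's own cost unused

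*Protocol article*

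**What the plan says.** **Model.** The section Analysis of secondary outcomes opens with "Secondary outcomes will be analysed using a mixed model ANOVA" and continues "The family will be introduced into the model as a random effect". All tests are two-sided. No outcome is excepted. The list in the Secondary outcomes section includes "mortality from an angioedema attack, mortality from another cause, number of ICU admissions per year", together with ED admissions, intubations, EMS interventions, working days lost, costs and SF-36. For the primary outcome, by contrast, the Analysis of primary outcome section specifies a generalised mixed model with a named non-Gaussian distribution.

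**Costs.** Health economics data sets out two separate categories. The first is "Call centre costs include freephone, training of EMS personnel and answering of calls (time spent and number of calls". The second begins "Patient care costs include consumption of hospital resources (admissions) and out-of-hospital resources" and goes on to working days lost and costs left to the patient; it has no call centre item. The Secondary outcomes section lists "number of working days lost and their duration, costs of patient care and SF-36 score". The analysis section says that "costs (hospital and ambulatory costs) of patient care and SF-36 will all be estimated in each arm for 2 years". The Abstract (Methods/design) and the Background present the socio-economic cost of management by the call centre, compared with usual practice, as part of what the trial evaluates.

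**The concern.** A mixed model ANOVA assumes roughly normal residuals with constant variance. Two of the outcomes are binary deaths. Intubations and ICU admissions are counts likely to be zero for most patients. For such data the variance depends on the mean, and p values and intervals from the linear model can be misleading. Mortality and intubation are outcomes where a chance p value below 0.05 would attract attention.

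The cost question is separate. Only intervention patients are given the call centre's number (Intervention arm; Usual practice arm). If the economic aim is answered with patient care cost alone, any saving in admissions is counted while the service meant to produce it is not charged.

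**Working it through.** **Inputs.** 100 patients per arm (Sample size calculation). That figure reproduces: (1.960 + 1.036)² × (0.88×0.12 + 0.68×0.32) / 0.20² = 72.5, and 72.5 × 1.4 = 101.6 per arm. It serves here only as n; the article gives no figure for any secondary outcome or cost. Event risks below are assumptions, and family and centre effects are left out.

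**Step 1: events in one arm only.** With x events against 0 and n = 100 per arm, the two-arm ANOVA is t = (x/n) / √(s² × 2/n), where s² = x(1 − x/n)/(2n − 2), on 198 degrees of freedom. For x = 4: s² = 4 × 0.96/198 = 0.01939, standard error = √(0.01939 × 0.02) = 0.0197, t = 0.04/0.0197 = 2.03, p = 0.044. Fisher's two-sided p is 2 × (100×99×98×97)/(200×199×198×197) = 0.121.

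| Events (100 v 100) | ANOVA p | Fisher exact p |
|---|---|---|
| 3 v 0 | 0.082 | 0.246 |
| 4 v 0 | 0.044 | 0.121 |
| 5 v 0 | 0.024 | 0.059 |
| 6 v 0 | 0.013 | 0.029 |

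The ANOVA p value is about 2 to 3 times smaller. The 4 v 0 and 5 v 0 splits fall below 0.05 only under ANOVA.

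**Step 2: calibration under no difference.** Simulated rejection rate at nominal 0.05 (40,000 trials per row, trials without events counted as non-significant), and the chance of no event in 200 patients, (1 − risk)²⁰⁰:

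| Assumed risk | ANOVA type I error | Chance of no event |
|---|---|---|
| 0.5 % | 0.002 | 37 % |
| 1 % | 0.014 | 13 % |
| 2 % | 0.039 | 2 % |
| 5 % | 0.043 | about 0 |
| 10 % | 0.052 | about 0 |

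With no event the residual variance is zero and the statistic is 0/0. For overdispersed counts (negative binomial, mean 0.02 to 0.2, dispersion parameter 0.1 or 0.5), a linear comparison rejected in 0.029 to 0.049 of null trials.

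**Step 3: cost items, section by section.**

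| Item | Health economics data | Secondary outcomes | Analysis of secondary outcomes |
|---|---|---|---|
| Call centre | collected, own category | not in the cost outcome | not in the cost outcome |
| Hospital and out-of-hospital care | patient care cost | included | included |
| Working days lost | patient care cost | included by that definition; also a separate outcome | outside the bracketed limit; still a separate outcome |
| Costs left to the patient | patient care cost | included by that definition | outside the bracketed limit |

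No listed outcome uses the call centre costs. If the centre cost C per year and served 100 trial patients, leaving it out lowers the intervention arm by C/100 per patient-year. Purely for scale, an assumed C of 50,000 to 500,000 currency units gives 500 to 5,000.

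**The case against.** The article condenses a fuller protocol, and an analysis plan or economic plan may say more. This carries weight for costs, where the article is silent on how items are combined. It carries less for the model: the article states a method, makes no exception, and names a generalised model for the primary outcome, so ANOVA is hard to read as shorthand.

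Some stronger readings are tempting, and the documents do not support them:

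- A reader might infer that every secondary p value is invalid or that false positives are inflated. The simulation shows rates at or below about 0.05 throughout. The fault is conservatism at very low risks, misleading p values at particular splits, and no test when there are no events.
- A reader might infer that ED outcomes are sparse too. The sample size section assumes 0.88 ED visits or admissions per control patient-year, combined, or 0.88 × 100 × 2 = 176 over two years. Nothing there marks ED visits as rare.
- A reader might infer that a linear model is wrong for costs. It compares arithmetic means, which is a defensible target; skewness calls for a more robust interval.
- A reader might infer that working days drop out. They remain a separate outcome; only their money value falls outside the bracketed limit. That limit stands in the analysis section alone, not in the outcome definition.
- A reader might infer that the cost outcome is biased towards the intervention as it stands. As a patient care cost it is narrow, not biased. It misleads only if read as the cost of the strategy.

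**Conclusion.** The point holds in two parts. The stated model is wrong for deaths and very rare events: at 100 per arm it turns a 4 v 0 split from p = 0.121 into p = 0.044, and it gives no test in 37 % of trials at an assumed 0.5 % risk or 13 % at 1 %. For commoner counts the case rests less on error rates than on having a rate per unit of follow-up. These figures rest on assumed risks and ignore family and centre.

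The cost part is a mismatch between what is collected, what is defined as the outcome and what is analysed. Its direction is clear if patient care cost is used to answer the economic aim: the intervention arm's cost is understated. Its size cannot be computed from the article, and the unseen economic plan may already deal with it. Both parts concern secondary outcomes; the change should be made, but the primary analysis does not depend on it.

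**What to change.** **Model.** Replace the single ANOVA sentence with a method for each type of outcome:

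- deaths and very rare events: counts per arm with exact intervals;
- other counts: Poisson or negative binomial mixed model with log follow-up time as offset;
- SF-36: linear mixed model, as now;
- costs: difference in mean cost with a skew-tolerant interval, for example by bootstrap.

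Account for the reference centre, the randomised unit, as well as family in the modelled comparisons. A bootstrap that resamples patients alone would not do this, and eight centres are few, so the method should be stated.

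**Costs.** Reconcile Health economics data, Secondary outcomes and Analysis of secondary outcomes. Define a total cost comparison that uses every patient care item listed under Health economics data and adds the call centre costs to the intervention arm. Report patient care cost alongside it.

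**Price.** Wording only, since every item is already planned for collection. The total cost result will be less favourable to the intervention than patient care cost alone, and some rare outcomes will be described without a model-based test.

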## Discussion

Key priority issues in HAE management are reducing morbidity and mortality rates and socio-economic costs [2]. No study has ever been conducted to determine whether a central dedicated call centre for HAE attacks would reduce morbidity and the socio-economic impact of the disease.

The indications for the specific treatment of HAE attacks are well established. Plasma-derived C1INH and icatibant are the undisputed emergency drugs for life-threatening cases (laryngeal involvement), abdominal attacks and cases with facial involvement [2, 3, 20, 21]. Early home treatment is recommended [2, 15]. HAE patients trained in icatibant self-administration can recognise HAE attacks and decide when to inject [22], thereby avoiding hospital admission [12]. In an evaluation of the feasibility and efficacy of plasma-derived C1-INH in 31 patients with HAE, the time from attack onset to start of treatment was significantly shorter after than before training in self-injection [23]. Nevertheless, morbidity remains high in these patients. In one retrospective study, 73 patients (16 %) presented at the hospital ED with an attack and 59 % were admitted to hospital [13]. In another, 21 patients (11 %) presented at the hospital ED with an attack [11]. According to a recent prospective study, most of these patients visited the ED because they were short of medication or because they were unaware that emergency treatment could be self-administered. Our prospective controlled cluster-randomised trial would enable evaluation of the impact of a measure (dedicated call centre) that might shorten the time from attack onset to first contact with a healthcare professional.

HAE is a considerable economic burden both to the healthcare system and to HAE patients and their families [13]. Reducing the number of hospital admissions might help reduce this burden. We hypothesise that the use of a dedicated call centre providing expert advice for HAE might significantly reduce the number of admissions (morbidity rate) and thus the socio-economic costs associated with the disease.

### Trial status

Recruitment for the trial was completed in June 2014.

